**Exclusion Criteria:**

- Those who are pregnant women, lactating women or planning to become pregnant during

the course of study.

- Those who are severely ill or more than two comorbidities
- Those who have any plan to migrate from the study area for at least 1 year
- HbA1c ≥93mmol/mol (10.5%)
- Those who are on insulin therapy

## **7.8. Study variables**

**Dependent variable:** HbA1c level

**Independent variables**

- - **Socio-demographic information (from Baseline):** Age, Sex, Education level, Occupation, Religion, Marital status, Residence, Smoking habit, and Alcohol habit
  - **Clinical and biochemical parameters (baseline end line):** HbA1c, fasting blood glucose, Systolic diastolic blood pressure, Lipid profile, Quality of life, Body mass index (BMI), Waist hip ratio (WHR), Physical activity level, Current medication used
  - **Dietary intake (baseline end line):** Carbohydrate, Fat, Protein, Food groups, Nutritional knowledge score on diabetes.

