# **Project summary (~250 words)**

Diabetes mellitus is one of the major intractable public health problems in developing countries including Nepal. The dietary approach is of paramount significance in the management of type 2 diabetes. There is still a lack of evidence on a dietitian-led dietary approach to the management of T2DM patients in the Nepalese context. The aims of this study is to examine the effectiveness of dietitian-led dietary approach to management of diabetes on reduction of HbA1c level, nutrition education score and macronutrient intake among T2DM patients in a tertiary care hospital in Kathmandu, Nepal.

The Dietary Approach to the Management of Diabetes (DIAM-D) trial is a hospital-based, open-label, two-armed, randomized control trial. A total of 156 participants with T2DM having HbA1c >6.5% will be enrolled in the study. Participants will be consecutively enrolled and assigned to receive nutrition education and counseling (NEC) and diet plan in the intervention group (n=78) and usual routine care in the control group (n=78) randomly. The NEC will be provided to participants on group session and the diet plan will be face-to-face individual basis at the time of enrollment and follow-ups will be done every month. Baseline data will be collected using a structured questionnaire for an interview and the biochemical tests will be measured. Baseline data will be collected at the time of enrollment, midline in three months and end-line data collection in 6 months. The primary outcome of the study will be a difference in mean change (from baseline, midline to 6 months) in the HbA1c level between the two study arms from baseline to end line. The secondary outcomes measure will be changed in biochemical and clinical parameters between the two arms at baseline midline to six months. Data will be entered using Epidata Software and transferred to the STATA/MP version 14.1 for further analysis. Data will be analyzed using an intention-to-treat basis. Independent sampele t-test will be used to estimates changes between the intervention and usual care arms.

**Key word:** Dietitian, Dietary approach, Management, Diabetes, Nepal

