# **Plan for data management and statistical analysis**

- **Data entry:** A data entry program will be developed using EpiData version 3.0. A number of skips and ranges will be developed to ensure data entry. Trained data entry professionals will enter the data. After the data entry, a thorough check and cleaning of data will be done to maintain consistency.
- **Data analysis:** Data will be analyzed on an intention-to-treat analysis. Data will be analyzed using STATA/MP version 14.1 (StataCorp LP, College Station, Texas). A number of statistical analysis will be done to analyze the data which are listed below:
- **Normality test:**The normality of data will be assessed using the Kolmogorov-Smirnoff test and visual inspection of Q-Q plots. Normally distributed data will be presented as means with standard deviation whereas non-normally distributed data will be expressed as medians with interquartile ranges.
- **Descriptive statistics**: Descriptive statistics will be carried out for socio-demographic information. Frequency, percentage, mean (standard deviation) and median (inter-quartile range) will be calculated under descriptive statistics.
- **Chi-square test**: Chi-square or Fisher exact test will be used to analyze between the intervention and usual care arm for categorical variables.
- **Independent sample t-test:** Difference between intervention and usual arm will be applied using independent sample t-test assuming equal variance if data is normally distributed for continuous variables (two-tailed; parametric).
- **Mann-Whitney U test**: Mann-Whitney U test will be used to compare the medians of continuous variables if in case the assumption for independent sample t-test will be violated (two-tailed; non-parametric).
- **Linear regression**: A linear regression analysis will be used to model the primary and secondary outcome measures.

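### Section 7.8 lists end-line outcomes, including HbA1c itself, as independent variables for HbA1c and omits randomised arm; a regression using that list would bias the treatment effect

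*Protocol*

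**What the plan says.** Protocol section 7.8 (Study variables) states: "Dependent variable: HbA1c level". Under the sub-heading for independent variables it gives three groups.

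- Demographic and habit variables, labelled "Socio-demographic information (from Baseline".
- A group labelled "Clinical and biochemical parameters (baseline end line", containing "HbA1c, fasting blood glucose, Systolic diastolic blood pressure, Lipid profile, Quality of life, Body mass index (BMI), Waist hip ratio (WHR", followed by physical activity and current medication.
- A group labelled "Dietary intake (baseline end line", containing "Carbohydrate, Fat, Protein, Food groups, Nutritional knowledge score on diabetes".

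Randomised arm is in none of the three.

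The section Plan for data management and statistical analysis says: "A linear regression analysis will be used to model the primary and secondary outcome measures". It names no covariates or time point and does not refer to section 7.8. The same section plans a two-tailed independent-sample t-test between arms, with Mann-Whitney U as the fallback. The Project summary names only the t-test: "Independent sampele t-test will be used to estimates changes between the intervention and usual care arms".

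Elsewhere many of the listed items are things the trial sets out to change or assess. The Specific objectives cover macronutrient intake, nutritional knowledge, biochemical parameters, BMI and waist-hip ratio. The hypothesis predicts better knowledge and macronutrient intake in the intervention arm. The Project summary makes change in biochemical and clinical parameters the secondary outcomes.

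**The concern.** In a randomised comparison the explanatory variable is the arm, and covariates should be fixed before randomisation. End-line diet, knowledge, weight and fasting glucose are measured after the intervention and may be changed by it. Diet and knowledge are the routes by which a dietitian-led programme is expected to lower HbA1c. A regression that holds them constant no longer estimates the whole effect of being assigned to the programme. It estimates what is left after those routes are closed, and it loses the protection of randomisation, because patients with the same end-line diet in the two arms need not be comparable in other respects.

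Listing HbA1c on both sides, without limiting the independent entry to baseline, is the extreme case. An adjusted analysis built this way could suggest little effect of an intervention that works. It could also disagree with the t-test, and the analysis section does not say which of the two is decisive.

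**Working it through.** **1. The text side by side.** Section 7.8 uses two timing labels: baseline only for demographics, and baseline plus end line for the clinical and dietary groups. Read literally under its heading, it admits end-line values as predictors of HbA1c. The analysis section offers no other covariates. The protocol has no second list of independent variables.

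**2. HbA1c as its own predictor.** If end-line HbA1c is the outcome and also a regressor, the fit is perfect and the arm coefficient is zero. If the outcome is change in HbA1c and both baseline and end-line HbA1c are regressors, their coefficients are -1 and +1 and the arm coefficient is again zero.

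**3. Other end-line covariates.** Let τ be the total effect of arm on end-line HbA1c, s the share passing through an end-line covariate M, and β the slope of HbA1c on M:

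- M = (sτ/β)·arm + u
- HbA1c = β·M + (1 - s)·τ·arm + γ·baseline HbA1c + e

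A model without M gives an arm coefficient of τ. A model with M gives (1 - s)·τ.

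**4. Inputs for a scale.** The protocol gives no effect estimate for the regression to reproduce. From its sample size section I take d = -0.64 and 54 per arm. The printed S = 0.1 cannot serve as the SD here: 2 × (1.96 + 1.282)² × 0.1² / 0.64² = 0.51, or 1 per arm, not 54. The SD that matches 54 per arm is 0.64 × √27 / 3.242 = 1.03. That mismatch is a separate matter.

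Assumptions not in the documents: SD 1.03; within-arm correlation of M with HbA1c 0.6 (β = 0.6 × 1.03 = 0.618); correlation of baseline with end-line HbA1c 0.5 (γ = 0.515); M independent of baseline HbA1c; no unmeasured common cause of M and HbA1c.

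**5. Results, 4,000 simulated trials per row, 54 per arm.**

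| Share s through M | Unadjusted: estimate, power | Baseline HbA1c only: estimate, power | Baseline HbA1c plus M: estimate, power |
|---|---|---|---|
| 0% | -0.64, 0.90 | -0.64, 0.96 | -0.64, 1.00 |
| 25% | -0.64, 0.89 | -0.64, 0.96 | -0.48, 0.96 |
| 50% | -0.64, 0.89 | -0.64, 0.96 | -0.32, 0.69 |
| 75% | -0.65, 0.90 | -0.64, 0.96 | -0.16, 0.22 |
| 100% | -0.64, 0.89 | -0.64, 0.96 | 0.00, 0.05 |

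Hand check at s = 50%: residual SD = 1.03 × √(1 - 0.36 - 0.25) = 0.643. The arm shift in M is 0.5 × 0.64 / 0.618 = 0.518, so the variance inflation is 1 + 0.518²/4 = 1.067. The standard error is 0.643 × √(2/54) × √1.067 = 0.128, and 0.32 / 0.128 = 2.50. Power is about Φ(2.50 - 1.98) = 0.70, in line with 0.69.

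Power does not fall at small s, because M also removes residual variance. The bias is there at every s above zero.

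**The case against.** A reader might infer that the planned regression will adjust away the intervention effect. The documents do not support that, for three reasons.

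- The regression sentence names no covariates and does not point to section 7.8. The link is an inference. Covariate choice is often left to a statistical analysis plan, which is not shown here.
- The timing labels can be read as a measurement schedule. Section 7.10 describes dietary assessment at baseline and end line in that sense, and the questionnaire headings use the same pairing. That HbA1c appears in the list favours this reading, since nobody would intend to regress HbA1c on itself.
- The between-arm comparison named in the Project summary and the analysis section is an unadjusted t-test or Mann-Whitney U, which no covariate list can affect.

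Nor does the missing arm entry mean that arm is left out of the analysis. Arm is the comparison in the summary, the objectives and the t-test, and the questionnaire records it.

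All of this stands, and it makes the point conditional. It does not remove it. On the schedule reading, section 7.8 still classes trial outcomes as independent variables and omits the explanatory variable. The finding is not that covariates are unspecified; it is that the one list the protocol does give assigns the wrong roles.

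**Conclusion.** The point holds in conditional form. Section 7.8 misclassifies post-randomisation outcomes as independent variables and leaves out randomised arm. If the linear regression of HbA1c draws end-line values from that list, its arm coefficient loses the share of the effect passing through them: from none to all, and exactly all if end-line HbA1c enters as in step 2. The documents do not give that share, and the table rests on the assumptions listed with it.

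A reader might want a narrower figure. If end-line fasting glucose shares HbA1c's 0.63 SD shift and correlates 0.5, 0.6 or 0.8 with it within arm, the coefficient is 0.63 × (1 - correlation) = 0.32, 0.25 or 0.13 SD. That is a 50% to 80% loss, with power near 43%, 34% and 18% at 54 per arm. This should not be quoted as the size of the problem. It needs an SD near 1.0 that the protocol does not print, treats glucose as a parallel marker and not a mediator, and assumes correlations the documents do not supply.

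The t-test or Mann-Whitney comparison stands. What is at risk is the adjusted estimate and its agreement with that comparison.

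**What to change.** In section 7.8, name randomised arm as the explanatory variable and restrict the covariates to baseline values, with baseline HbA1c included. Move the end-line clinical, biochemical, dietary and knowledge items to a list of secondary outcomes. If the timing labels were meant only as a measurement schedule, say so and place them under data collection.

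In the analysis section, add that the regression for the treatment effect contains arm and baseline covariates only, and that any model with end-line covariates is exploratory mediation and not an estimate of effectiveness.

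The cost is an edited list and a sentence or two. Data collection, sample size and patient care do not change, and baseline HbA1c is already measured. Under the assumptions above, adjusting for it raises power from about 0.90 to 0.96 without biasing the estimate.

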## **7.9. Expected time and duration of the study**

The study will be carried out for six months, from baseline data collection, follow-up midline data collection and end-line data collection for outcome measure.

## **7.10. Tools and techniques for data collection**

The baseline and end-line data collection will be performed in both intervention and usual care arm. A pre-tetsed culturally accepted and adapted, Nepali translated version tools and techniques will be used to conduct the study. A total of three data collection team who have graduated in health or nutrition science will be hired from the local area.

**Tools and procedure**

- Screening checklist: This checklist entails information regarding inclusion and exclusion criteria.
- Baseline questionnaire: The study participants’ information on Socio-demographic, such as age, sex, occupation, educational level, residence, religion, ethnicity, etc. will be taken by using a face-to-face structured questionnaire interview. The questionnaire will be adopted from NDHS 2017 and STEP Survey 2019^22,23^.
- Dietary intake: Dietary intake assessment will be assessed before intervention (baseline) and after intervention (end line) using 24-hour qualitative dietary recall and food frequency questionnaire (FFQ) to compute the macronutrient intake level.
- Biochemical measurements: A fasting blood sample for HbA1c, fasting glucose, liver function test (bilirubin, ALT, AST ALP, and albumin) and lipid profile (total cholesterol, triglycerides, HDL, LDL) will be measured at baselines, three months and six months. All blood samples will be taken and handled, analyzed and disposed of according to local practice policy.
- Quality of life: The Problem Areas in Diabetes (PAID) score^24^, a 20 items questionnaire measuring the problems related to emotions, treatment, food and social support, will be measured at baselines and 12 months.
- Physical measurement: Height will be measured using a stadiometer to the nearest 1cm. Participants' weight will be measured to the nearest 0.1kg using the Seca weighing scale. BMI will be measured calculated using the widely used formula (BMI= weight (kg)/height (m)^2^), and waist Hip Circumference (WHR) will be measured using measuring tape. Systolic and diastolic blood pressure will be measured three times after 5 minute seated rest using a sphygmomanometer and stethoscope. The trained data enumerator will be taking physical measurements according to the study manual procedures.
- Nutritional knowledge score on diabetes: The diabetes knowledge test (DKT)^25^will be used to assess the nutritional knowledge score on diabetes.
- Physical activity: The physical activity will be measured using the Global Physical activity questionnaire recommended by WHO STEPwise surveillance tools^23^.
- Monitoring checklist: This will be used as every month follow up checklist. The information on lifestyle modification such as consumption of food, physical activities, adherence, and diabetic-related minor and major complication will be sought.

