## **Specific objectives:**

- To measure the change in HbA1c level among T2DM patients between the intervention and control/usual care arm.
- To evaluate the change in macronutrient intake level among T2DM patients in the intervention and usual care arm.
- To assess dietitian-led nutrition education and counseling on nutritional knowledge of diabetes among T2DM patients.
- To evaluate the change in biochemical parameters among T2DM patients in the intervention and usual care arm.
- To assess the nutritional status such as BMI and WHR among T2DM patients

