# **Research questions/hypothesis**

Dietitian-led dietary approach to the management of diabetes will improve on HbA1c level, nutrition knowledge score and macronutrient intake level compared to usual care among type 2 diabetes mellitus patients in tertiary care hospital in Nepal.

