## **7.11. Management protocol of patients/participants if applicable**

In the intervention phase, the educational and diet plan package will be developed. All the intervention packages will be approved by a multi-disciplinary expert team comprising an endocrinologist and dietitian prior to the intervention. Patients in the usual care arm will receive routine care as to how he/she is practicing in their daily life. Routine care includes general knowledge on diabetes disease process, blood glucose monitoring, a healthy lifestyle, preventing treating diabetes complications and developing personalized strategies for the decision-making process ^26^. The intervention package will include mainly two-phase, nutritional counseling emphasis on lifestyle modification of diabetes patients and individual basis diet plan for each T2DM patients for intervention arm. The nutrition education and counseling and individual diet plan will be applied by trained dietitians.

In the first phase, participants in the intervention arm will receive a nutrition counseling session. Nutrition counseling package consists of six modules (knowledge about diabetes and additional information, treatment of diabetes, food-based dietary guidelines, and exercise guidance, knowledge of hypoglycemia treatment, foot care, medication, and blood glucose monitoring)^12,16^ which will be developed as a training manual and approved by multi-disciplinary expert team. Nutritional counseling will be provided by a dietitian who had to work at the participating working center. Every month, follow-up will be done to reemphasize the key message.

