| 3 | Food-based dietary guidelines, healthy eating pattern | Dietary guidelines for each food group such as starch, fruits and vegetables and additional information on diabetes.  A nutrition education brochure will be provided. Information will be emphasis on healthy eating habits such as information about glycemic index and glycemic load of food, the difference between simple and complex carbohydrate, difference between saturated  and unsaturated fat, total calorie intake according to their needs, and calorie contains in beverage and alcohol  Overview of food groups and their roles in the body. |
| 4 | Diet planning: serving size and meal frequency | Guidelines of serving size and meal frequency and its importance  Demonstration: serving size (household measurement) |
| 5 | Knowledge of hypoglycemia treatment  and foot care | Guidelines of knowledge of hypoglycemia and its treatment knowledge of foot care practices |

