**Section 6: Diabetes Knowledge Questionnaire (DKQ), Baseline/End line**

| **Items** | **Questions** | **Yes** | **No** | **I don't know** |
| --- | --- | --- | --- | --- |
| 1 | Eating too much sugar and other sweet foods is a cause of diabetes. |  |  |  |
| 2 | The usual cause of diabetes is lack of effective insulin in the body. |  |  |  |
| 3 | Diabetes is caused by failure of the kidneys to keep sugar out of the urine. |  |  |  |
| 4 | Kidneys produce insulin |  |  |  |
| 5 | In untreated diabetes, the amount of sugar in the blood usually increase. |  |  |  |
| 6 | If I am debates, my children have a higher chance of being diabetic |  |  |  |
| 7 | Diabetes can be cured. |  |  |  |
| 8 | A fasting blood sugar level of 210 is too high. |  |  |  |
| 9 | The best way to check my diabetes is by testing my urine. |  |  |  |
| 10 | Regular exercise will increase the need for insulin or other diabetes medication. |  |  |  |
| 11 | There are two main types of diabetes: Type 1 (insulin-dependent) and Type 2 (non-insulin-dependent) |  |  |  |
| 12 | An insulin reaction is caused by too much food. |  |  |  |
| 13 | Medication is more important than diet and exercise to control my diabetes. |  |  |  |
| 14 | Diabetes often causes poor circulation |  |  |  |
| 15 | Cuts and abrasions on diabetic heal more slowly. |  |  |  |
| 16 | Diabetics should take extra care when cutting their toenails. |  |  |  |
| 17 | A person with diabetes should cleanse a cut with iodine and alcohol |  |  |  |
| 18 | The way I prepare my food is as important as the foods I eat. |  |  |  |
| 19 | Diabetes can damage my kidneys |  |  |  |
| 20 | Diabetes can cause loss of feeling in my hands, fingers, and feet |  |  |  |
| 21 | Shaking and sweating are signs of high blood sugar |  |  |  |
| 22 | Frequent urination and thirst are signs of low blood sugar. |  |  |  |
| 23 | Tight elastic hose or socks are not bad for diabetics. |  |  |  |
| 24 | A diabetic diet consists mostly of special foods |  |  |  |

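### The outcome called nutrition knowledge would be scored with a general diabetes knowledge form: 3 to 5 of its 24 items concern diet, and none tests the taught dietary topics

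*Protocol*

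**What the plan says.** The hypothesis (Protocol, Research questions/hypothesis) is that the dietitian-led approach "will improve on HbA1c level, nutrition knowledge score and macronutrient intake level compared to usual care". The Expected outcome section repeats the claim. One of the specific objectives is "To assess dietitian-led nutrition education and counseling on nutritional knowledge of diabetes among T2DM patients". The Project summary and General objectives use a third label, a nutrition education score. Section 7.8 lists the knowledge score under dietary intake.

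For measurement, section 7.10 (Tools and procedure) cites the DKT, which "will be used to assess the nutritional knowledge score on diabetes". The items of that test are not in the protocol. The questionnaire at the end of the protocol contains one knowledge form, headed "Section 6: Diabetes Knowledge Questionnaire (DKQ), Baseline/End line". It has 24 statements answered yes, no or don't know. No scoring rule and no diet sub-score are printed.

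Table 1 in section 7.11 sets out what is taught. Module 3 covers food groups, glycaemic index and load, simple against complex carbohydrate, saturated against unsaturated fat, and calories. Module 4 covers "Guidelines of serving size and meal frequency and its importance". Modules 1, 2 and 5 cover the disease and its complications, its treatment, hypoglycaemia and foot care.

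**The concern.** The label on the outcome and the content of the form do not match. If the total is reported as nutrition knowledge, a difference between arms will be read as showing that patients learned about diet. The form could show such a difference with no change on any diet item. Conversely, patients could learn what modules 3 and 4 teach and the score would not register it, because no item asks about it.

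The instrument itself is also unsettled, since the methods text and the printed form carry different names. What is at stake is one of the three hypothesised effects, and it is not the primary one.

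**Working it through.** No published figure has to be reproduced here. The check is a count of the printed items against the taught content.

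**Inputs.** The 24 items of Section 6 of the Main Study Questionnaire; the topics of modules 1 to 5 in Table 1 (section 7.11).

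**Step 1: items that mention eating, food or diet.** These are items 1, 12, 13, 18 and 24.
- Item 1 ("Eating too much sugar and other sweet foods is a cause of diabetes") is about cause.
- Item 12 is about what brings on an insulin reaction.
- Items 13 (medication against diet and exercise), 18 (food preparation) and 24 (nature of a diabetic diet) concern diet as management.

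Broad count: 5/24 = 20.8%. Narrow count: 3/24 = 12.5%.

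**Step 2: the other 19 items.**

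| Content | Items | Number |
| --- | --- | --- |
| Cause, physiology, heredity, types, course | 2, 3, 4, 5, 6, 7, 11 | 7 |
| Glucose level and testing | 8, 9 | 2 |
| Exercise | 10 | 1 |
| Complications | 14, 15, 19, 20 | 4 |
| Foot and wound care | 16, 17, 23 | 3 |
| Signs of high or low sugar | 21, 22 | 2 |
| Total | | 19 |

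Non-diet share: 19/24 = 79.2% on the broad count of diet items, 21/24 = 87.5% on the narrow count.

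**Step 3: items on the listed topics of modules 3 and 4.** Glycaemic index or load, carbohydrate type, fat type, calories, food groups, serving size, meal frequency: 0/24. Items 18 and 24 touch module 3's general theme of healthy eating, but only loosely.

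**Step 4: can the total move without the diet items?** Yes. Module 1 teaches causes, types, clinical features, insulin action and complications. Module 2 teaches the role of drugs and exercise. Module 5 teaches hypoglycaemia and foot care. The counselling text of section 7.11 adds blood glucose monitoring. Much of the content in Step 2 is therefore taught in the intervention arm. If each item counts one point (an assumption, as no scoring rule is printed), up to 19 of 24 points can change while all five diet items stay the same.

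**Step 5: does another form fill the gap?** No. The Perceived Dietary Adherence Questionnaire (Section 7 of the questionnaire) mentions low glycaemic index foods and carbohydrate spacing, but it counts days of reported behaviour, not knowledge. The 24-hour recall measures intake.

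**The case against.** The best defence is that the protocol's construct is broader than dietary knowledge. It speaks of nutritional knowledge in relation to diabetes, and the education package is itself largely general diabetes education. A general form suits modules 1, 2 and 5 and can validly show a change in diabetes knowledge. That stands, and it is a good reason to rename the outcome. It does not rescue the present label, which the protocol sets beside macronutrient intake and files under dietary intake.

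Scoring rules may also sit in an analysis plan that is not shown, and item-level answers are recorded, so the diet items could be examined separately. That is fair as to scoring. But no later plan can score questions on modules 3 and 4 that were not asked at baseline.

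Four stronger readings are tempting, and the documents do not support them:
- **That the trial as a whole cannot show what it claims.** HbA1c is the primary outcome, and macronutrient intake has its own instruments.
- **That the comparison of total scores lacks power because a few diet items are diluted by 19 others.** This needs the other 19 items to show no gain, although the intervention teaches much of their content. The protocol also gives no standard deviation or expected gain for the score.
- **That most items are taught in both arms.** The protocol says "Routine care includes general knowledge on diabetes disease process, blood glucose monitoring, a healthy lifestyle", which is too general for an item-by-item comparison.
- **That a sub-score of the five diet items would solve the problem.** Those items test none of the listed module 3 and 4 topics either, and two of them are about cause and insulin reaction.

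**Conclusion.** The point holds for the nutrition-knowledge claim only. On the printed form, 12.5% to 20.8% of the items concern diet and none tests the listed dietary topics. A between-arm gain in the total would show improved diabetes knowledge; it would not by itself show improved nutrition knowledge.

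The conclusion assumes that the printed DKQ is the form used. If the DKT named in section 7.10 is used instead, the count does not carry over, because its items cannot be checked here. The contradiction between the two names is itself a defect to be settled. The judgement on which items count as dietary leaves a range of 3 to 5, and the conclusion is the same at either end.

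**What to change.** 1. Name one instrument throughout, so that section 7.10 and Section 6 of the questionnaire agree, and print that instrument.
2. Call its total diabetes knowledge wherever it now appears as nutrition knowledge or a nutrition education score: Project summary, General and Specific objectives, Research questions/hypothesis, section 7.8, section 7.10 and Expected outcome.
3. If a nutrition-knowledge claim is to be kept, add a short prespecified block of items on the module 3 and 4 topics, ask it in both arms at baseline and end line, and rest the claim on that block alone.

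The first two changes are wording. The third adds a few minutes to each interview and needs pre-testing, which the protocol already plans for its questionnaire. It has to be in place before baseline interviews begin.
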